This is further specified into the following sub-objectives:2a. To compose ‘*patient profiles*’ according to ‘adherence to a particular recommendation’, ‘readiness for change’, and ‘need for support’;To describe which *patient profiles* are most prevalent per time point;To describe *socio-demographic and clinical characteristics* of the most frequent patient profiles.2b. To assess personal, clinical, and cancer-related *modifiable determinants* of *adherence*, *readiness for change*, and *need for support* in PMBC survivors over time;To gain knowledge on which determinants should be targeted to promote sustained adherence;To describe *modifiable determinants* of the most frequent patient profiles.2c. To select Behavior Change Techniques [30] that could be used to influence the associated modifiable determinants (i.e., toolbox containing potential intervention ingredients).2d. To explore the *acceptability of the selected Behavior Change Techniques*, and to explore *perceptions on the optimal method* to promote (sustained) adherence among PMBC survivors, oncology health care professionals, and other relevant stakeholders.

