#### Quantitative measures

*Overweight and body fat distribution*. Excess body weight and body fat distribution will be determined by self-reported *height* and *weight* with which we calculate BMI [15] and self-measured *hip- and waist circumference* [40]*.* The waist circumference and waist/hip ratio provides an indication of body fat distribution (i.e. abdominal fat accumulation) and associated disease risk [41].*Physical activity and sedentary behaviour**Physical activity* will be assessed with the Physical Activity Scale for the Elderly (PASE) [42], a 13-item questionnaire that assesses participation in leisure activities. In addition, muscle strengthening activities will be recorded, as well as time spent on paid or unpaid work, and household activities [43]. The PASE has shown to have good to excellent test–retest reliability, and to be a reasonably valid method to classify healthy elderly individuals and cancer patients into categories of physical activity [43–45].Detailed data on participants’ *physical activity and sedentary behaviours* will be collected using an accelerometer, the ActiGraph wGT3X [46]. Survivors treated in a hospital selected for wearing the accelerometer will wear an accelerometer on their wrist for 7 consecutive days on their non-dominant arm. Upon return of the ActiGraph, the data will be downloaded using the accompanying software ActiLife (Version 6.13.3; ActiGraph, Pensacola, FL, USA) and saved in raw format. Subsequently, the.gt3x files are converted to time-stamp free.csv files which could be exported into R v.3.6.0. The.csv files are processed using the R-package GGIR v.2.1-0 [47, 48]. Data of participants will be excluded from subsequent analysis if their accelerometer files demonstrated a post-calibration error bigger than 0.01 g; if there are less than 3 valid wear-days (defined as ≥ 16 h per day) [49]; or if there are no wear data present for each 15 min period of the 24 h cycle. Physical activity level will be expressed as average acceleration across the day (Eucledian Norm Minus One (ENMO), mg) [49], intensity gradient across the day (IG), average time accumulated in low intensity physical activity (LPA) per day (min/day), average time accumulated in moderate-to-vigorous physical activity (MVPA) per day (min/day), average time accumulated in vigorous physical activity (VPA) per day (min/day), time spent inactively per day (min/day), and most active continuous 30 min (M30) per day.*Five-Times-Sit-to-Stand (FTSTS) test)*: this test will be used to determine lower body muscle function, and may indicate sarcopenia and frailty [50]. Participants will perform this test at home using a chair and a stopwatch (included in the information package). Participants will measure the time it takes to stand up and sit down five times from a chair. This test has been found valid and reliable to assess lower body muscle function [50].*Dietary intake**Food diary**: **Dietary intake* will be assessed by asking the patients to complete an online food diary (the ‘Eetmeter’, a digital tool of the Netherlands Nutrition Center) to register all foods and drinks, in portion sizes or gram/ml, they have consumed during the day [51]. At wave 2 and wave 3, patients will be asked to register their daily intake during three days: two week days and one weekend day. The Eetmeter is connected to the Dutch Food Composition Database (NEVO) [52, 53] which allows for the calculation of the quantity of daily energy, micro-, and macronutrients (i.e., fat, protein, and carbohydrate) consumption automatically.*Adherence to dietary guidelines: Diet quality* will be assessed by use of the Dutch Healthy Diet index-15 (DHD-15) [54]. The DHD-15 is a brief food frequency questionnaire that estimates diet quality and assesses adherence to the fifteen food-based Dutch dietary guidelines of 2015 (e.g., fruit, vegetables, wholegrain products, legumes, nuts, diary, fish, tea, fats and oils, coffee, red and processed meat, sweetened beverages and fruit juices, alcohol, and salt). Per component, the scores range from 0 to 10, resulting in a total score between 0 (no adherence) to 150 (complete adherence). The ability of the DHD-15 to rank persons on their diet quality is considered to be acceptable [54]. Several of the Dutch Dietary Guidelines are similar to the WCRF recommendations, therefore, the results of the DHD-15 will also provide insight into adherence to the WCRF recommendations.*Smoking**Smoking* will be assessed by standardized questions on smoking habits (i.e., cigarettes/shag, cigars, pipe tobacco, and e-cigarettes). PMBC survivors will be classified in; never, ex, light, and heavy smokers.*Sleep**Sleep quality and disturbances* will be measured using the Pittsburgh Sleep Quality Index (PSQI) [55] which assesses sleep quality and disturbances over a one-month period. Nineteen items measure seven ‘component’ scores: subjective sleep quality, sleep latency, sleep duration, habitual sleep efficiency, sleep disturbances, use of sleeping medication, and daytime dysfunction. The sum of these seven component scores add up to one global score. The total global component score ranges from 0 to 21. Higher scores indicate lower sleep quality and more sleep disturbances [55]. The PSQI is known for its good validity, it is able to discriminate good from poor sleepers. In addition, internal homogeneity and consistency (test–retest reliability) are good.Detailed data on participants’ *sleep pattern* will be collected by use of an accelerometer, the ActiGraph wGT3X [46]. Participants will wear the accelerometer during the night (in total 7 nights) to obtain data on: sleep duration, sleep latency, wake after sleep onset, sleep interruptions, and sleep efficiency.*Lifestyle and health related measures*For each single lifestyle recommendation, the following possible changeable determinants of adherence will be determined.*Readiness for lifestyle change* will be measured according to the transtheoretical model (not ready: pre-contemplation/contemplation); (ready: preparation/action/maintenance); (relapse: relapse) [29] and will be assessed for each recommendation with a single item.For each of the lifestyle recommendations, participants will be asked to indicate which stage of change fits their current state or their state just before diagnosis (i.e., wave 1) best with self-designed questions (see Table 1). If patients have attempted to change but could not maintain this change, they automatically relapse to a prior stage of the transtheoretical model. For this reason they will be allowed to tick boxes of two stages of change, both ‘relapse’ and either ‘precontemplation’, ‘contemplation’, or ‘preparation’ [29, 31].*Perceived need for support.* At all measurement points and for each specific lifestyle and body weight recommendation, participants will be asked if they are in need for support to be able to change their lifestyle and/or body weight. Also, they will be asked to specify the type of support they would prefer by use of an open-ended question.*Biological markers in relation to lifestyle and bodyweight.*Blood will be collected by venipuncture at the participants’ treating hospital. All participants, in 9 out of 16 participating hospitals, will receive a lab form in their information package (at wave 2 and wave 3). Attached to this lab form, they will receive a short questionnaire. This questionnaire contains questions concerning fasted state, medication use, and sickness at the moment of blood sampling, as these factors can have an impact on the biological markers of interest. Time of blood donation will be marked on the questionnaire. Directly after blood sampling, the serum blood sample will be allowed to clot at room temperature and will be centrifuged. The EDTA blood sample will be centrifuged at room temperature directly after blood sampling. The subtracted plasma, serum, and buffy coat samples will be processed within 2 h of collection and are stored at − 80 °C until further analyses. All procedures will be defined in a protocol to ensure standardisation over study sites. All blood samples will be transported from the laboratory at the treating hospitals to the Biobank Maastricht. Following, appropriate ELISAs and ILLUMINA analyses will take place to determine the biological markers. Blood samples will be stored in a biobank for later analysis of biomarkers. Analysis of the following biomarkers is anticipated:*Inflammation*. Pro- and anti-inflammatory cytokines will be determined, including Tumor Necrosis Factor-alpha (TNFα), Interleukin-6 (IL-6), Interleukin-10 (IL-10), and Interleukin-1 Receptor Antagonist (IL-1Ra), and a general marker of inflammation C-reactive protein (CRP).*Metabolism:* biomarkers include leptin, insulin, insulin growth factor-1, glucose, glycated haemaglobin (HbA_1_C_1_), total cholesterol, triglycerides, High-Density-Lipoprotein (HDL) cholesterol, Low-Density-Lipoprotein (LDL) cholesterol, and vitamin D.Clinical cancer-related variablesData on clinical cancer-related variables will be retrieved from the Netherlands Cancer Registry (NCR), which records clinical data of all newly diagnosed cancer patients in the Netherlands.

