### Data analyses

#### Quantitative data

Descriptive statistics and Generalized Linear Mixed Models (GLMM) will be used to: (1a) longitudinally assess proportions of (non-)adherence to each recommendation, readiness for change, and the need for support, to (1b) examine sociodemographic and clinical characteristics, and to (1c) examine biological determinants, of those who do not adhere and of those in need for support over time. The relation between adherence to each recommendation and socio-demographic and non-changeable clinical characteristics will be longitudinally assessed by fitting GLMM with adherence to each recommendation (no/yes) as dependent dichotomous variable and time (wave1, wave2, wave3) and socio-demographic and clinical characteristics (age, ethnicity, socioeconomic status, marital status, stage of cancer at diagnosis, type of treatment) as independent variables. We will assess the need to include interaction terms between time and the socio-demographic and clinical characteristics. These analyses will be repeated for need for support as outcome variable. Similar analyses will be conducted for biological determinants of cancer prognosis modifiable by lifestyle and bodyweight.

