With regard to aim 2a, for each single lifestyle recommendation ‘patient profiles’ will be composed by creating a cross tabulation of the variables ‘adherence to a particular recommendation’ (yes/no), ‘readiness for change’ (Not ready: pre-contemplation/contemplation; ready: preparation/action/maintenance), and ‘need for support’ (yes/no) for each time point (see “Appendix”). Based on these cross tabulations, it will be examined which patient profiles are most prevalent per time point. In addition, descriptive statistics will be used to describe changeable socio-demographic (e.g., employment, education) and clinical characteristics (e.g., tumor stage, treatment received) of the most frequent patient profiles. GLMM will be used to assess socio-demographic and clinical modifiable determinants of adherence, readiness for change, and need for support, as captured by the most prevalent patient profiles over time (aim 2b). We will assess the need to include interaction terms between time and the socio-demographic and clinical characteristics. Based on the behavior change technique taxonomy [30], the changeable socio-demographic and clinical determinants will be matched to suitable behaviour change techniques (aim 2c). Additionally, with respect to aim 2a and 2b, the composition of ‘patient profiles’, multilevel latent class modelling will be used combining adherence to all recommendations, readiness for change to each specific recommendation, and need for support for each specific recommendation, for each time point for all recommendations. The multilevel latent class model will be used to gain insight into the course of the patient profiles over time.

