## Appendix: Overview of the categorization of cancer survivors into ‘Patient Profiles’ according to adherence to a particular WCRF-recommendation, stage of change, and perceived need for support.

**Table Taba:**

**Stage of change** [29]		Adherence to a particular WCRF-recommendation	
		Does not meet recommendation	Meets recommendation
*Not ready for change*			
*Precontemplation* (*not ready*): not intending to take action in the next six months	No need for support	Cancer survivors who do not meet a WCRF-recommendation, do not intend to change their behavior, and do not perceive a need for support	Cancer survivors who meet a WCRF-recommendation, do not intend to change their behavior, and do not perceive a need for support
	Need for support	Cancer survivors who do not meet a WCRF-recommendation, do not intend to change their behavior, and perceive a need for support^a^	Cancer survivors who meet a WCRF-recommendation, do not intend to change their behavior, and report a perceived need for support^a^
*Contemplation* (getting ready): intending to take action in the next 6 months	No need for support	Cancer survivors who do not meet a WCRF-recommendation, intend to change in the foreseeable future, and do not perceive a need for support	Cancer survivors who meet a WCRF-recommendation, intend to change in the foreseeable future, and do not perceive a need for support
	Need for support	Cancer survivors who do not meet a WCRF-recommendation, intend to change in the foreseeable future, and perceive a need for support	Cancer survivors who meet a WCRF-recommendation, intend to change in the foreseeable future, and perceive a need for support
*Ready for change*			
*Preparation (ready)*: ready to take action in the next 30 days	No need for support	Cancer survivors who do not meet a WCRF-recommendation, intend to take action in the immediate future, and do not perceive a need for support	Cancer survivors who meet a WCRF-recommendation, intend to take action in the immediate future, and do not perceive a need for support
	Need for support	Cancer survivors who do not meet a WCRF-recommendation, intend to take action in the immediate future, and perceive a need for support	Cancer survivors who meet a WCRF-recommendation, intend to take action in the immediate future, and perceive a need for support

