*Action*: has made overt lifestyle changes in the past 6 months	No need for support	Cancer survivors who do not meet a WCRF-recommendation, but have made overt lifestyle changes in the past 6 months, and do not perceive a need for support	Cancer survivors who meet a WCRF-recommendation, have made overt lifestyle changes in the past 6 months, and do not perceive a need for support
	Need for support	Cancer survivors who do not meet a WCRF-recommendation, but have made overt lifestyle changes in the past 6 months, and who perceive a need for support (to maintain lifestyle changes)	Cancer survivors who meet a WCRF-recommendation, have made overt lifestyle changes in the past 6 months, and who perceive a need for support (to maintain lifestyle changes)
*Maintenance*: doing a new behavior for more than six months	No need for support	Cancer survivors who do not meet a WCRF-recommendation, but have been maintaining lifestyle changes for at least 6 months, and who do not perceive a need for support	Cancer survivors who meet a WCRF-recommendation, have been maintaining lifestyle changes for at least 6 months, and who do not perceive a need for support
	Need for support	Cancer survivors who do not meet a WCRF-recommendation, but have been maintaining lifestyle changes for at least 6 months, and who perceive a need for support to maintain their changes	Cancer survivors who meet a WCRF-recommendation, have been maintaining lifestyle changes for at least 6 months, and who do not perceive a need for support to maintain their changes

^a^Unlikely scenario, expected cell-frequency of near zero.

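### The stage-of-change scheme has no place for women who have always met a recommendation, so whole-cohort readiness proportions mix women who need no change with women unwilling to change

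*Protocol article*

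**What the plan says.** The Appendix of the protocol article sorts women by stage of change, need for support and whether they meet a given recommendation. Precontemplation stands under the block 'Not ready for change' and is defined by intention alone: "not intending to take action in the next six months". In the 'meets recommendation' column of that row is the cell "Cancer survivors who meet a WCRF-recommendation, do not intend to change their behavior, and do not perceive a need for support". The footnote that marks cells expected to be almost empty is not attached to it.

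Maintenance, in the 'Ready for change' block, is defined as "doing a new behavior for more than six months". Its cells for adherent women begin "Cancer survivors who meet a WCRF-recommendation, have been maintaining lifestyle changes for at least 6 months". The action cells likewise require a recent overt change.

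Under Quantitative measures, readiness "will be assessed for each recommendation with a single item". The items are self-designed. A double tick for relapse is described, but no option for women who have always met the recommendation.

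The Abstract lists readiness for change among the primary outcomes. Under Data analyses, Quantitative data, descriptive statistics and mixed models are to "longitudinally assess proportions of (non-)adherence to each recommendation, readiness for change, and the need for support", with no restriction by adherence. The same section collapses readiness to ready versus not ready, crosses it with adherence and need for support to form profiles, and ties the determinant models to those profiles.

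**The concern.** Take a lifelong non-smoker. She has adopted no new behaviour, so action and maintenance do not describe her. She plans no change, so the definitions place her in precontemplation, in the block labelled 'not ready'. Another lifelong non-smoker may read the item differently and tick maintenance, which counts as 'ready'. Neither answer measures readiness, because neither woman has anything to change.

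Two results are exposed. First, the proportion ready in the whole cohort depends on how adherent women tick an item that does not fit them, and it can move between waves because adherence moves. Second, within the 'meets recommendation' column the ready/not-ready split may reflect how the item is read. Since the plan describes and models the most prevalent profiles, an arbitrary split of long-standing adherers can change which profile appears most prevalent.

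**Working it through.** **1. Do the definitions leave a gap?** Apply each stage to a woman who has always met the recommendation and plans no change.

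| Stage | What it requires | Does she fit? |
|---|---|---|
| Precontemplation (not ready) | no intention to act | yes |
| Contemplation (not ready) | intention within 6 months | no |
| Preparation (ready) | action within 30 days | no |
| Action (ready) | overt change in past 6 months | no |
| Maintenance (ready) | new behaviour for over 6 months | no |
| Relapse | a change tried and not maintained | no |

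Only a 'not ready' cell fits. The protocol recognises such women: its smoking classes include never smokers.

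**2. The plan's own figure.** The Sample size section assumes 18.6% smokers and requires (16 × 10)/0.186 = 860.2, stated as 860. It reproduces. The figure is not disputed; it supplies the prevalence used below.

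**3. Whole-cohort share 'not ready'.** Let A be the share who adhere, q the share of adherers classed not ready, and r the same share among non-adherers. Then

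P(not ready) = A × q + (1 − A) × r.

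The derivative with respect to A is q − r. Unless q equals r, the proportion moves whenever adherence moves, even with r constant.

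**4. Bounds for smoking, per 1000 women.** Smokers 186, non-smokers 814. Assume r = 0.5 (not in the document), giving 93 smokers not ready.
- All non-smokers tick precontemplation (q = 1): (814 + 93)/1000 = 90.7%.
- All non-smokers tick maintenance (q = 0): 93/1000 = 9.3%.

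Readiness among smokers is 50% in both cases.

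**5. A milder version.** Ex-smokers may validly be in action or maintenance. Assume, again from outside the document, that 25–75% of non-smokers never smoked (about 204 to 610 women), that ex-smokers tick maintenance, and that 30–50% of smokers are ready.
- Never smokers in precontemplation, lowest 'ready' share: 0.186 × 0.3 + 0.814 × 0.25 = 25.9%.
- Never smokers in precontemplation, highest: 0.186 × 0.5 + 0.814 × 0.75 = 70.4%.
- Never smokers in maintenance: 0.186 × 0.3 + 0.814 = 87.0% to 0.186 × 0.5 + 0.814 = 90.7%.

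When never smokers are in precontemplation, they make up 61% (0.2035/0.3337) to 87% (0.6105/0.7035) of everyone counted as not ready.

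**6. What restricting to non-adherers does to model size.** With 186 smokers per 1000, the smaller readiness group is at most 186/2 = 93. The plan's rule of 10 per variable asks for 160 with 16 determinants, so 93 supports at most 9.

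**The case against.** The strongest reply is that the plan already separates adherent women. The Design section first asks whether a woman needs to change at all, and answers this by adherence. Every profile contains adherence, so a never smoker in precontemplation and a smoker in precontemplation occupy different cells. The latent class model also combines adherence with readiness. This stands: in the profiles, readiness among non-adherent women remains interpretable.

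Four stronger readings are tempting, and the document does not support them.
- *The determinant models lose their meaning.* Objective 2b does name readiness, and adds "To gain knowledge on which determinants should be targeted to promote sustained adherence". However, the analysis section describes the models for determinants "as captured by the most prevalent patient profiles over time (aim 2b"), and those profiles include adherence. No whole-cohort readiness model is clearly planned.
- *Behaviour change techniques will be matched to women who need none.* The Design section assigns techniques by profile, and adherent and non-adherent women are in different profiles.
- *The timing conclusion rests on a readiness curve.* Sub-objective 1a names only non-adherence and need for support. Table 1 links readiness to 2a, 2b and 2c. Timing also draws on the interviews, focus groups and Delphi study.
- *The 9.3% to 90.7% range forecasts the error.* It assumes that all non-smokers tick the same box and that half of the smokers are ready. Smoking is also the extreme case: the other smallest groups in the Sample size section range from 25.66% to 45.6%.

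It is also fair that the wording of the self-designed items is not shown, so where long-standing adherers will place themselves is an inference. The reply does not reach the readiness proportions planned for the whole cohort, or the ready/not-ready split inside the 'meets recommendation' column.

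**Conclusion.** The concern holds in a limited form. As published, the scheme gives long-standing adherers no stage except one labelled 'not ready'. Three things are affected: the readiness proportions over time that are not restricted by adherence, any readiness model fitted to the whole cohort, and the ready/not-ready split among adherers, with its possible effect on which profile appears most prevalent. Readiness among non-adherent women within the profiles is not affected.

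The potential size is large where most women adhere. For smoking, 814 of 1000 women are placed on a scale that may not fit them, and with the assumed 50% among smokers the cohort share 'not ready' is bounded only by 9.3% and 90.7%. The smoking prevalence is the protocol's. The smokers' readiness and the way adherers answer are assumptions, so the numbers show how weakly the proportion is tied to the readiness of the women who need to change, and not what will be observed.

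**What to change.** 1. Report readiness per wave and per recommendation among women who do not meet that recommendation, or stratified by adherence. Do the same in any model with readiness as the outcome.
2. Relabel the precontemplation cell for adherent women as 'meets recommendation, no change intended', and do not count it as 'not ready'.
3. In the profiles, do not interpret the ready/not-ready split among adherers as readiness. For smoking, never versus ex status, already collected, can separate lifelong adherers. For other recommendations recoding cannot fully identify lifelong adherers who tick maintenance, which is why using non-adherent women as the denominator is the safer choice.

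The cost is recoding and wording, with no new data. The downside is a smaller denominator, about 186 per 1000 for smoking. A readiness model restricted to smokers could not carry 16 determinants under the plan's own rule of 10 per variable. It should use fewer (at most 9 per 1000 recruited, under an even split) or be descriptive only.
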